### Randomization and Blinding

Randomization will occur at the baseline visit at a ratio of 2:1 intervention versus control. Randomization will be stratified to achieve balance in treatment allocation across idiopathic and CD-related fistula types. Because the total sample size is 12, randomization will be blocked using blocks of size 3 (2:1 intervention to control) within each stratum (idiopathic versus CD-related). Based on historical clinical data we anticipate enrolling 9 Chron’s participants and 3 idiopathic participants. Blinding of the patients, surgeons other than the investigator performing the procedure, and study team members assessing outcomes to study arm allocation will be employed to reduce bias in conducting study activities and evaluations. Given that the control group will be receiving a routine care procedure, the investigator who will be performing all procedures will be unblinded to the treatment assignment for each participant. To maintain blinding while assessing outcomes, clinical exams during follow-up study visits will be performed by another surgeon not involved in the initial screening visit or the procedural encounter. In the case of a serious adverse event or medical emergency in which knowledge of the treatment is necessary for the participant’s well-being or medical care, the unblinded investigator will be alerted to ensure appropriate medical management.

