### Administration

The following procedures will be performed by the surgeon for administration of the intervention.

A clinical examination under anesthesia with an anal fistula probe will be conducted to rule out active infection, anal stenosis, or active proctitis and confirm the presence of a single fistula tract.The seton will be removed, the fistula tract curetted vigorously to remove granulation tissue lining the tract, and the tract will be flushed with saline.The fistula tract length and diameter and amount of the sphincter muscle involved will be assessed by the surgeon with an anal fistula probe placed from the external to the internal opening.The appropriate model collagen matrix will be used based on the length of the tract.The collagen will be saturated with the rhPDGF solution in a sterile dish for a minimum of 10 min.After the collagen is fully saturated with rhPDGF, it will be pulled through the fistula tract carefully from the internal opening to the external opening.The collagen will be sutured to the rectal mucosa at the internal opening and any portion beyond the skin level will be trimmed to sit flush with the external opening.

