#### Secondary and Tertiary Outcomes Analysis

The secondary efficacy and safety endpoints will be analyzed for all randomized participants, as appropriate. Analyses will not be dependent on the findings of the primary endpoint. The first secondary endpoint considers all treatment-related adverse events and the proportion of participants with such events by arm will be analyzed/reported in the same way as the primary endpoint. The proportion will then be compared across arms using Fisher’s Exact test. If there are at least two participants with multiple treatment-related adverse events, a Mann-Whitney test will compare the number of adverse events per participant across arms.

The next secondary endpoint is fistula healing at Month 3 measured as a binary variable. The probability of healing in each arm will be calculated as the proportion of randomized participants per arm that are diagnosed as completely healed by a clinical evaluation of no visible drainage from the external opening at the Month 3 follow-up visit. The endpoint will be modeled as the outcome in a logistic regression model, conditioning on the treatment arm and baseline etiology. The effect will be presented as an adjusted odds ratio with a 95% confidence interval, as well as the marginal risk ratio after performing standardization. A p-value less than 0.05 will be considered statistically significant, but interpretation will be primarily focused on the 95% confidence interval. Residuals will be inspected to inspect model fit and validity of the homoscedasticity assumption. If model fit is poor, a Fisher’s Exact test will be used in place of logistic regression. Missing data are expected to be limited but will be handled using multiple imputation. Individuals who are lost to follow-up before Month 3 will also be included via the multiple imputation procedure, considering plausible imputations conditional on their baseline and Month 1 follow-up assessments, as well as weekly symptom data. The primary analysis will be modified intention-to-treat (ITT) based on randomized arm, as the investigational product is not available to patients who are not randomized to treatment before the Month 3 outcome assessment. It will be modified ITT in the sense that only participants who receive the investigational intervention will be analyzed as part of the intervention arm; this is necessary as some exclusion criteria cannot be assessed until the time of surgery.

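### The modified ITT rule removes non-recipients from the intervention arm with no matching rule for controls, so the Month 3 healing comparison can be biased, and it conflicts with the stated healing denominator

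*Protocol article*

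**What the plan says.** All references are to the Protocol article.

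- **Analysis set.** Secondary and Tertiary Outcomes Analysis calls the analysis modified intention-to-treat: "It will be modified ITT in the sense that only participants who receive the investigational intervention will be analyzed as part of the intervention arm". The justification follows: "this is necessary as some exclusion criteria cannot be assessed until the time of surgery". Nothing equivalent is said for the control arm.
- **Denominator.** The same section opens with "The secondary efficacy and safety endpoints will be analyzed for all randomized participants, as appropriate" and defines the probability of healing as "the proportion of randomized participants per arm that are diagnosed as completely healed".
- **Timing and blinding.** Randomization and Blinding states: "Randomization will occur at the baseline visit at a ratio of 2:1 intervention versus control". One investigator performs all procedures and is unblinded.
- **Check at the procedure.** The first step under Administration is: "A clinical examination under anesthesia with an anal fistula probe will be conducted to rule out active infection, anal stenosis, or active proctitis". It also confirms that there is a single tract. Exclusion Criteria adds anatomical limits to securing the plug disk, which are a surgical judgement.
- **Control procedures.** Under Efficacy Assessments, controls with Crohn's disease have seton removal and debridement only. Idiopathic controls also receive a commercial plug.
- **Other rules on who counts.** Recruitment and Consent counts only those who undergo the baseline procedure and stops follow-up of consented participants who are not treated. Screen Failures includes people in whom the device could not be placed. Participant Discontinuation/Withdrawal lets the investigator withdraw someone in whom an exclusion criterion is recognized late. All three are worded for both arms.

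**The concern.** The stated reason for the modification makes sense only if some participants are assigned first and found unsuitable afterwards. Those assigned to the intervention then leave the analysis. For a control with the same finding, no rule says so. Randomization made the two arms comparable, and an exclusion applied after it to one arm undoes that. The person who judges the finding also knows the assignment. Blinded assessment at follow-up cannot repair a selection made in the operating room.

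Two comparisons are exposed: healing at Month 3, and recurrence at Month 6, which is analysed by the same procedures. Both are secondary. However, healing also informed the sample size, and the Discussion says the results will guide a larger trial. With 8 against 4 participants, one removal is visible in the estimate.

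The same section also gives two denominators for one endpoint: everyone randomized per arm, and, for the intervention arm, recipients only.

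**Working it through.** **Who can leave the set.** Randomization and Blinding expects 9 participants with Crohn's disease and 3 with idiopathic fistulas, in blocks of 3 at 2:1 within each stratum. That gives 9/3 = 3 Crohn's controls and 3/3 = 1 idiopathic control. The three Crohn's controls have no device, so failure to place one cannot make them screen failures, and they do undergo the baseline procedure. The idiopathic control could leave if the plug cannot be placed. The withdrawal rule could reach any control, but it is discretionary and concerns withdrawal from the study, not the analysis set.

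**Reproducing the plan's bounds.** Inputs from Sample Size: 2/4 healed on control, and 7/8 or 8/8 on the intervention. I take the Carlin-Louis interval as independent Beta(1,1) priors with equal-tailed 95% limits of the posterior difference, and check it with posterior mean - 1.96 SD.

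- 7/8 v 2/4: Beta(8,2) and Beta(3,3). Mean difference 0.80 - 0.50 = 0.30. Variance 0.01455 + 0.03571 = 0.05026, SD 0.224. Lower bound 0.30 - 1.96 x 0.224 = -0.139; by quantiles -0.144. Stated: -0.14.
- 8/8 v 2/4: -0.011 by the same formula, -0.008 by quantiles. Stated: -0.01.

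Both reproduce.

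**Effect of removing non-healers from the intervention arm only** (bounds by quantiles):

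| Everyone randomized | Difference | Lower bound | After removal | Difference | Lower bound |
|---|---|---|---|---|---|
| 7/8 v 2/4 | 0.375 | -0.14 | 7/7 v 2/4 | 0.50 | -0.03 |
| 6/8 v 2/4 | 0.25 | -0.26 | 6/6 v 2/4 | 0.50 | -0.06 |
| 4/8 v 2/4 | 0 | -0.47 | 4/7 v 2/4 | +0.07 | -0.42 |
| 4/8 v 2/4 | 0 | -0.47 | 4/6 v 2/4 | +0.17 | -0.37 |

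Sample Size reads -0.14 as confidence against substantial harm and -0.01 as confidence of benefit. One removal moves the bound from -0.144 to -0.032. That is 0.112 of the 0.136 between -0.144 and -0.008, or about 82% of the distance.

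**Expected bias when the treatment has no effect.** Let q be the share of the intervention arm removed and h the healing probability of those removed. Overall healing is 50%, and no control is removed. Bias = (0.5 - q x h)/(1 - q) - 0.5. The documents give neither q nor h, so both are assumed, with q equal to 1 or 2 of 8.

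| q | h = 0 | h = 0.25 | h = 0.50 | h = 0.75 |
|---|---|---|---|---|
| 0.125 | +0.07 | +0.04 | 0.00 | -0.04 |
| 0.25 | +0.17 | +0.08 | 0.00 | -0.08 |

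The sign depends on h: positive below 0.50, negative above it.

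**The case against.** The strongest reply has four parts.

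**The rule may be less one-sided than it reads.** The exclusion criteria cover everyone, and the provisions on the baseline procedure, screen failure and late-recognized exclusions are not limited to one arm. This stands in part. A reader might infer that only intervention participants can ever be removed; the article does not establish that, and the idiopathic control in particular could leave. But none of these provisions clearly removes a Crohn's control from the analysis.

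**The direction is not known.** A reader might infer that the comparison is certainly biased towards the intervention. That goes beyond the article, which reports neither how often surgery reveals a disqualifying finding nor how such patients heal. Poorer healing with infection, proctitis or extra tracts is plausible, and no more than that.

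**The contradiction may be only apparent.** The sentence on all randomized participants is qualified, and a specific rule after a general one is a normal way to write. That softens the opening sentence. It does not rescue the healing definition, which names randomized participants per arm for this very endpoint.

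**Healing is secondary in a 12-participant pilot.** The 7/8 v 2/4 interval runs from about -0.14 to 0.72, so a shift of 0.07 or 0.125 is small beside it, and the Discussion admits limited power. That is fair. But imprecision does not justify an avoidable bias, and Sample Size does attach conclusions to the lower bound.

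A reader might also add the predictability of small fixed blocks. That is a separate matter and would require the operator to know the block size, which the article does not say. It adds nothing here, since the operator knows each assignment at surgery anyway.

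**Conclusion.** The point holds in this form: the plan states a post-randomization exclusion for the intervention arm, gives no counterpart for controls, and leaves the triggering judgement to an unblinded operator. For about 3 of the 4 expected controls, failed implantation cannot occur. The healing and recurrence comparisons can therefore be biased, probably in favour of the intervention if those removed would have healed less often, and against it if they would have healed more often.

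One removed non-healer raises the difference from 0.375 to 0.50 in the plan's own scenario, and from 0 to +0.07 when there is no effect. These sizes assume that one or two of the 8 are removed, that they do not heal, and that no control is removed. The lack of a matching rule and the conflict over the denominator do not depend on those assumptions.

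The primary endpoint is defined on those assigned to treatment, so it is not affected as written. It would be if participants without implantation were set aside as screen failures: by Clopper-Pearson, 7/8 has a lower bound of 0.47 and 7/7 has 0.59.

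**What to change.** 1. Make the primary analysis of Month 3 healing all randomized participants in the arm assigned, and carry the same set into the recurrence analysis.
2. Keep a modified set only as a sensitivity analysis, with the surgical exclusions defined identically in both arms, whether or not an implant was planned.
3. For participants still to be enrolled, open the allocation only after the examination under anesthesia has confirmed eligibility. Exclusions at surgery then fall before randomization in both arms.
4. Reconcile Recruitment and Consent, Screen Failures, Primary Outcomes Analysis, and Secondary and Tertiary Outcomes Analysis on who counts. In particular, anyone randomized but not treated needs a Month 3 healing assessment, whereas the present text ends follow-up for consented participants who are not treated.

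Cost: a protocol amendment, allocation opened in the operating room, and Month 3 follow-up of any randomized participant who is not implanted. The estimate may be slightly less favourable to the intervention. Enrollment began in November 2024, so item 3 may reach few participants; items 1, 2 and 4 apply to all of them.

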### Recruitment and Consent

This study aims to recruit 12 participants, that are adults >21 years of age regardless of gender, race, or ethnicity. There is no information currently available regarding differential agent effects in participants defined by race or ethnicity. No vulnerable populations are expected to be enrolled in this study. The target number of patients to be screened for enrollment is 60 with the expectation of enrolling and randomizing ~25% of those screened and accounting for discontinuation, withdrawal, and loss to follow-up. This will be a single-site study at VUMC with an anticipated accrual rate of 1–2 participants per month.

Existing patients, new patients, and provider-referred patients with a diagnosis of a complex perianal fistula that is not amenable to a fistulotomy can be recruited for this trial. Patients that are interested in the trial will be scheduled for a screening visit where they will sign written informed consent and undergo the baseline examination for eligibility. Informed consent is initiated prior to the individual’s agreeing to participate in the study and continues throughout the individual’s study participation. Informed Consent Forms (ICF) will be VUMC Institutional Review Board (IRB)-approved. Only those participants who undergo the baseline procedure will be considered treated and count towards total participant population. Participants who signed consent but did not receive treatment will not be followed further.

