#### Screen Failures

Screen failures are defined as participants who consent to participate in the clinical trial but are not subsequently randomized or the device is unable to be implanted. A minimal set of screen failure information is required to ensure transparent reporting of screen failure participants, to meet the Consolidated Standards of Reporting Trials (CONSORT) publishing requirements and to respond to queries from regulatory authorities. Minimal information includes demography, screen failure details, eligibility criteria, and any serious adverse event (SAE).

Individuals who consent and do not meet the criteria for participation in this trial (screen failure) because of the following criteria may be rescreened once the below criteria have been resolved.

No draining seton in placeActive infectionSurgical procedures outlined in the exclusion criteriaParticipation in an investigational study as outlined in exclusion criteriaPregnant or breastfeeding

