### Outcomes

#### Primary outcome

The primary outcome of this study will be to evaluate the technical performance of rhPDGF-enhanced collagen implantation for treatment of complex perianal fistulas. This will be measured by the proportion of participants with procedural success as defined by implantation of the intervention without any intervention-related serious adverse events (SAEs) within 3 months of the procedure. The 3-month endpoint is the average timepoint when the surgeon makes the diagnosis that the perianal fistula has completely healed or failed to heal.

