#### Primary Outcomes Analysis

The primary endpoint is technical performance of the treatment. This will be reported as the proportion of participants assigned to the treatment arm with successful implementation of the treatment (without SAEs). This will be reported along with a Carlin-Louis 95% confidence interval.

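### Failed implantations can be excluded after randomization by an unblinded operator, which cannot happen to Crohn's controls; this can bias Month 3 healing and inflate the primary success proportion

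*Protocol article*

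**What the plan says.** Five places in the Protocol article bear on this.

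- **Secondary and Tertiary Outcomes Analysis.** The analysis is modified intention-to-treat in that "only participants who receive the investigational intervention will be analyzed as part of the intervention arm". The reason given is that "this is necessary as some exclusion criteria cannot be assessed until the time of surgery". Nothing equivalent is stated for controls. The same section also says that secondary endpoints use all randomized participants as appropriate, and that the healing proportion is taken over those randomized to each arm.
- **Screen Failures.** A screen failure is a consented participant who is "not subsequently randomized or the device is unable to be implanted". Failed implantation is therefore listed as a case separate from never being randomized.
- **Recruitment and Consent.** "Only those participants who undergo the baseline procedure will be considered treated and count towards total participant population", and "Participants who signed consent but did not receive treatment will not be followed further".
- **Randomization and Blinding.** Randomization takes place at the baseline visit, and "the investigator who will be performing all procedures will be unblinded to the treatment assignment for each participant". The expected mix is 9 Crohn's and 3 idiopathic participants, in blocks of 3 within stratum.
- **Primary outcome and Primary Outcomes Analysis.** Success is "implantation of the intervention without any intervention-related serious adverse events" within 3 months, reported as "the proportion of participants assigned to the treatment arm with successful implementation of the treatment".

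Under Efficacy Assessments, Crohn's controls have the seton removed and the tract debrided with no implant, while idiopathic controls receive a commercial plug.

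**The concern.** The reason given for the modified rule makes sense only if some participants are randomized before all exclusion criteria have been checked. The check is then made by someone who knows the assignment, and one criterion (any anatomical obstacle to securing the plug disk) is a matter of surgical judgment. On paper the anatomical exclusions apply to both arms. An implant that cannot be placed, however, can occur only where one is attempted, and that is never the case for Crohn's controls.

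Two results are exposed. Month 3 healing would compare an intervention arm selected for implantable tracts with a control arm mostly not selected that way. Blinded follow-up examination cannot undo selection that took place in the operating room. The primary endpoint is a measure of technical performance: if a failed implantation becomes a screen failure and leaves the count, its implantation component cannot fail, and only a related serious adverse event can lower it.

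Because untreated participants are not followed, an analysis of all randomized participants may not be recoverable later.

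**Working it through.** **Who can be excluded for a failed implantation.** At 2:1, 9 Crohn's participants give 6 intervention + 3 control, and 3 idiopathic participants give 2 + 1. An implant is attempted in 6 + 2 = 8 of 8 intervention participants and in 1 of 4 controls.

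**The plan's own figures (Sample Size).** When x = n, the Clopper-Pearson 95% lower bound is 0.025^(1/n). For 8/8 this is 0.025^(1/8) = 0.631, matching the stated 0.63. The healing bounds reproduce if the Carlin-Louis interval is read as an equal-tailed interval for the difference of two independent Beta(1+x, 1+n−x) posteriors. The uniform prior is an assumption. Against 2/4 this gives −0.145 for 7/8 (stated about −0.14) and −0.008 for 8/8 (stated −0.01).

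**Primary endpoint, one failed implantation, no related serious adverse event.** For x < n the Clopper-Pearson lower bound is the 2.5% quantile of Beta(x, n−x+1). The Beta column is the 2.5% quantile of Beta(1+x, 1+n−x), because Primary Outcomes Analysis names a Carlin-Louis interval.

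| Case | Result | Clopper-Pearson lower | Beta lower |
|---|---|---|---|
| Not replaced, failure counted | 7/8 = 87.5% | 0.473 | 0.518 |
| Not replaced, failure dropped | 7/7 = 100% | 0.590 | 0.631 |
| Replaced, failure counted | 8/9 = 88.9% | 0.518 | 0.555 |
| Replaced, failure dropped | 8/8 = 100% | 0.631 | 0.664 |

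The last row is the plan's own planning scenario. The article does not say whether such participants are replaced, so both cases are shown.

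**Month 3 healing against 2/4, one failed implantation.** The starting point is the plan's 7/8.

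| Case | Intervention healed | Difference | 95% lower bound |
|---|---|---|---|
| All 8 assigned kept | 7/8 | 0.375 | −0.145 |
| One dropped who would not have healed | 7/7 | 0.500 | −0.031 |
| One dropped who would have healed | 6/7 | 0.357 | −0.183 |
| Replaced, as analysed | 7/8 | 0.375 | −0.145 |
| Replaced, all 9 counted, ninth not healed | 7/9 | 0.278 | −0.224 |
| Replaced, all 9 counted, ninth healed | 8/9 | 0.389 | −0.113 |

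All these intervals include zero. The dropped participant can move the bound either way.

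**How often, and how large a bias.** The article gives no failed-implantation rate, so the following is an assumed range. The chance of at least one failure among 8 is 1 − (1−f)^8: 34%, 57%, 83% and 90% for f = 5%, 10%, 20% and 25%. Suppose there is no treatment effect and 50% heal in both arms. If a fraction f of the intervention arm is dropped and those participants would heal with probability q, healing among the rest is (0.5 − f·q)/(1 − f). With q = 0 this is 0.5/0.9 = 55.6%, 0.5/0.8 = 62.5% and 0.5/0.75 = 66.7% for f = 10%, 20% and 25%, a spurious gain of about 6 to 17 points. With q = 0.25 the gain is about 3 to 8 points. With q = 0.5 it is zero, and with q above 0.5 it changes sign.

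**The case against.** The strongest reply concerns the primary endpoint. Primary Outcomes Analysis uses those assigned to the treatment arm, Sample Size plans on all 8 assigned, and implantation is itself part of success. Read alone, these keep a failed implantation as a counted failure. Someone examined under anesthesia with the seton removed has also arguably undergone the baseline procedure. This stands as far as it goes: the article contains both readings. But Screen Failures names the failed implantation explicitly, and nothing says which text governs.

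On healing, the same section refers to randomized participants per arm. That contradicts the modified rule, which is the more specific statement in the same paragraph and so most likely governs.

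The order of randomization and examination is inferred. The article says only that randomization occurs at the baseline visit, and the unabridged protocol, not shown here, may fix the order. If the allocation is already opened after the examination, much of the remedy is in place.

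The asymmetry is also limited to failed implantation. Branching, proctitis or infection can be found at surgery in a Crohn's control too, and the withdrawal rules apply to both arms. The count of 8 of 8 against about 1 of 4 therefore does not describe every exclusion at surgery.

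Finally, this is a 12-person pilot that acknowledges limited power. That softens the consequence for healing, but the technical-performance proportion is the primary outcome and is meant to guide a larger trial.

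**Conclusion.** The concern holds. Followed as written, the rules can remove randomized intervention participants after an unblinded operator fails to place the implant, while Crohn's controls, expected to be 3 of the 4 controls, cannot be removed for that reason. One such event changes the primary result from 87.5% to 100% (Clopper-Pearson lower bound 0.47 to 0.59) or, with replacement, from 88.9% to 100% (0.52 to 0.63). The direction is upward for the primary endpoint and unknown for healing.

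This rests on randomization preceding the operative check, which the text implies but does not state, and, for the primary endpoint, on the screen-failure and counting rules prevailing over the assigned-arm denominator. The frequency is unknown, and the figures are a sensitivity display, not an estimate of bias. Confidence is medium. The change should be made because most of it is cheap. The difference between collagen and no implant that the Discussion acknowledges is a separate matter and would remain.

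**What to change.** For participants not yet treated:

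1. Complete and record the examination under anesthesia, the operative eligibility check (same criteria in both arms), and the tract preparation and measurement before the allocation is opened. Anyone failing at that point is a screen failure in neither arm.
2. Analyse everyone whose allocation was opened in the assigned arm, and follow them to Month 3 even if nothing was implanted. Recruitment and Consent needs amending for this.
3. Count a failed implantation in the intervention arm as a primary failure, and limit Screen Failures to participants whose allocation was not opened.

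For participants already treated, report by arm every randomized participant excluded at surgery, with the reason, and add an analysis of all randomized participants. Where Month 3 status was not collected, show the result under both healed and not healed.

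Costs: this is a mid-trial amendment. Enrollment began in November 2024 with about 15 months planned, so if few participants remain, mainly the counting and reporting parts help. The collagen soak could add up to about 10 minutes under anesthesia in intervention cases, possibly less, since Administration already places it after measurement. Syringes must reach room temperature beforehand in every case, so some will go unused. Screen-failure details are already required, so the extra reporting is mainly the split by arm.

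One limit remains. In blocks of 3 with one control, an operator who knows past assignments can deduce 2, 1 or 1 later assignments when the control comes first, second or third. The mean is 4/3 of 3, or about 44%. Late opening reduces foreknowledge without removing it.
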